### Pilot study phase

3.3

This phase of the study aims to demonstrate that enrolled participants from the new firefighter study population can maintain adherence to the HLS app for at least 3-6 months. We will recruit ~50 new firefighters (a separate cohort from those enrolled in the beta testing) and monitor their app usage. App metrics such as session duration, screen views, and user retention within the app will provide insights into how users interact with the app over time. This cohort of new firefighters for the pilot study phase will also assess the HLS app’s ability to maintain/improve HLS parameters (HLS scores, physical fitness, mental health (trauma/depression) screeners). For the purposes of this pilot study, we will conduct a small single arm trial which aims to obtain preliminary evidence of the efficacy of a novel digital intervention and to collect qualitative feedback from a subgroup of target users. Changes in HLS parameters throughout the pilot testing will be evaluated with repeated measures of health metrics pre-and-post app usage among those participants that engaged in the HLS app for 3-6 months. Namely, participants will receive the same lifestyle and mental health questionnaires and fitness test at the two time points: before using the HLS app and at the subsequent follow-up (i.e. 3-6 months after). Both adherence and efficacy results will be adjusted for the potential influence of new firefighters’ demographic characteristics. Effect modification analysis will include fire crew, station and department cultures/policies (measured by the “Health Culture” score as mentioned below in 3.3.4.).

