### Participant incentives

3.5

Aim 1 was conducted on a volunteer basis by the research team and fire service expert panel with no formal compensation for the alpha and pre-beta testing of the development phase. For Aim 2 on usability (beta testing) among 50 enrolled new firefighters, we will conduct Focus Groups via Cambridge Health Alliance (CHA) Google Meet (expected n=25) compensated with a gift card, and satisfaction surveys (expected n=30) compensated by a gift card to get additional “end-user” feedback. For Aim 3, ~50 new firefighters will be recruited for pilot testing and their app usage will be monitored if they have completed more than three months of use (expected n=50). Upon completion of the pilot phase, participants will be given an additional gift card for a follow-up collection of health measures to compare against their baseline values.

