In the pilot study phase, Aim 3, adherence to the HLS app will be measured continuously as the total number of engagements with the software by each participant over the 3 to 6-month pilot study. This outcome will be supported by other prespecified app-usage metrics facilitated by the Managed IT Services provider (i.e. app user information; sign-ins, quest completion rate for each level, frequency of habit tracker use, and number of missions initiated). The primary outcome for validating the efficacy of the HLS app among the new firefighters’ will be the changes in the HLS score, comparing the participants’ pre- and post- app-usage scores (10). Using a behavior change measure (i.e. HLS score) as a primary outcome is justified in an intervention of short duration (11). As secondary outcomes, we will evaluate changes in 1-min pushups and mental health parameters. In addition, we will examine whether the health culture in various fire service workplace environments, as measured by the Health Culture score, influences the intervention effect of the app on the primary and secondary outcomes.

Generalized linear models will be utilized to assess the effect of the proposed app intervention comparing pre and post HLS scores, mental health scores, and 1-min push-up capacity upon completion of 3-6 months of app usage. All models will have their assumptions verified, using analysis of the residuals and other diagnostic testing. Generalized linear modeling will be used to model changes over time after taking into consideration the specific variance-covariance structure of repeated measurements or using other statistical methods such as generalized estimating equations models. All models will be adjusted for demographic and working conditions and other potential confounders. Interaction terms will also be incorporated into the models to evaluate any potential effect modification by working conditions, cultures, and policies. Statistical significance for all analyses will be considered as a two-tailed *p*<0.05.

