The creation of the app prototype was preceded by extensive literature reviews and even a qualitative study by our research team in order to investigate how to best accommodate the needs of our target population and how to best address potential facilitators and barriers to adherence to an HLS intervention (26). The educational content of the app was mainly derived from firefighter-specific resources and the graphics for the wireframes were designed to be firefighter-themed, where applicable. We also made sure that the daily workload associated with the app would be flexible enough to incur behavioral changes but not interfere with the work demands and busy lifestyle of professional firefighters. Most importantly, once pre-beta testing has been completed, the app will be evaluated by focus groups consisting of experienced firefighters at first and new firefighters after beta testing. Their feedback and ideas will then be used to optimize the app prototype before the pilot study phase and to ensure that the final version fits the end-users’ needs.

In order to counteract the high attrition and low long-term engagement rates traditionally associated with app-based interventions, we have employed multiple gamification strategies, a scoring system *(surviving* and *thriving* points*)* as well as the inclusion of a habit tracker and community missions (81). Other aspects targeting user engagement include goal setting, notifications that reinforce healthy behaviors, a leaderboard to compare users’ progress, levels and incremental challenges for the individual, team-based challenges, and allocation of points, coins, and badges for milestones) which have been shown to incentivize engagement, foster behavioral changes more effectively and make the use of an app more appealing (82, 83).

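### The primary pre-post HLS change is evaluated only in participants who stayed engaged for 3-6 months, and the article contradicts itself on whose app use is monitored

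*Protocol article*

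**What the plan says.** **Efficacy set.** Section 3.3 assesses change in HLS parameters by "repeated measures of health metrics pre-and-post app usage among those participants that engaged in the HLS app for 3-6 months". Section 3.6 models the pre-post comparison "upon completion of 3-6 months of app usage", and the follow-up column of Table 1 is likewise headed by 3-6 months of engagement. Section 3.6 names the change in HLS score as the primary efficacy outcome and sets two-tailed p<0.05. The trial has a single arm.

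**Adherence.** Section 3.3 aims to show that "enrolled participants from the new firefighter study population can maintain adherence to the HLS app for at least 3-6 months". It continues: "We will recruit ~50 new firefighters (a separate cohort from those enrolled in the beta testing) and monitor their app usage", and it lists user retention among the app metrics. In section 3.6, "adherence to the HLS app will be measured continuously as the total number of engagements with the software by each participant". Section 3.5 reads differently. About 50 are recruited, and "their app usage will be monitored if they have completed more than three months of use (expected n=50").

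**Attrition.** The Discussion describes the app's engagement features as a response to the "high attrition and low long-term engagement rates traditionally associated with app-based interventions". Its limitations paragraph covers self-report, performance and social-desirability bias, and short duration. It does not mention attrition or selection.

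**The concern.** Whether someone keeps using a lifestyle app for months is itself an outcome of being offered it. It plausibly shares a cause, motivation, with the lifestyle change being measured. Restricting the analysis to those who stayed describes completers, not the new firefighters who were offered the app. With no control arm, nothing in the data would reveal the selection. The article's premise is that habits slip after graduation, and success is framed as maintaining or improving. If those whose habits slip are the ones who stop opening the app, leaving them out could make decline look like maintenance.

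The section 3.5 wording raises a second problem. If monitoring started only after three months of use, the study could not answer its own question about retention among those enrolled.

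Both matter because the Discussion says this research will support using the app in a multi-center controlled trial. Retention, and change among all those offered the app, are the inputs that planning needs. Follow-up that is never sought from low users cannot be recovered at analysis.

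**Working it through.** **1. The plan's own figure.** Recruited: about 50 (sections 3.3 and 3.5). Expected past three months: 50 (section 3.5). Implied retention = 50/50 = 100%. The article gives no dropout rate, SD, effect size or power, so no sample-size calculation can be reproduced.

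**2. What 50 completers would need.** Enrolment = 50/(1 − d), rounded up, for an assumed dropout d:

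| d | Enrolment for 50 completers | Completers from 50 enrolled |
|---|---|---|
| 10% | 56 | 45 |
| 20% | 63 | 40 |
| 30% | 72 | 35 |
| 50% | 100 | 25 |

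**3. Size of the selection effect.** The model is an assumption. Change has SD 1 and true mean 0 among all enrolled. A latent engagement score has correlation ρ with change. Only the top fraction r on engagement is analysed. Then

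bias = ρ × φ(c) / r, with c = Φ⁻¹(1 − r).

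- r = 0.8: c = −0.842, φ(c) = 0.280. Bias at ρ = 0.3 is 0.3 × 0.280/0.8 = 0.105 SD.
- r = 0.5: c = 0, φ(c) = 0.399. Bias at ρ = 0.3 is 0.3 × 0.399/0.5 = 0.239 SD.
- r = 0.3: c = 0.524, φ(c) = 0.348. Bias at ρ = 0.3 is 0.3 × 0.348/0.3 = 0.348 SD.

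A simulation of 20,000 trials of 50 enrolled per setting, with a paired t-test at two-sided 0.05 in those retained, gave these rejection rates:

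| Retained | ρ = 0.1: bias, rejection | ρ = 0.3: bias, rejection | ρ = 0.5: bias, rejection |
|---|---|---|---|
| 80% | 0.035 SD, 5% | 0.105 SD, 10% | 0.175 SD, 21% |
| 50% | 0.08 SD, 7% | 0.24 SD, 22% | 0.40 SD, 55% |
| 30% | 0.12 SD, 7% | 0.35 SD, 26% | 0.58 SD, 63% |

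At ρ = 0 the bias is zero and the rejection rate is about 5% at every retention level. At full retention there is no bias for any ρ. Analysing all 50 with complete follow-up also gives a null mean of 0 and about 5%.

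**4. Precision.** The 95% CI half-width for mean change, in SD units, is t(0.975, n−1)/√n. For n = 50 it is 2.010/7.071 = 0.28. For n = 25 it is 2.064/5 = 0.41. For n = 15 it is 2.145/3.873 = 0.55.

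**5. Monitoring, side by side.** Section 3.3 monitors everyone recruited and lists retention as a metric. Section 3.6 counts engagements for each participant. Section 3.5 monitors those past three months. Under section 3.5 alone, three-month retention among those monitored is 100% whatever the true value. The engagement count is not fixed by that rule, because someone past three months can still have many or few engagements.

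**The case against.** A reader might infer that app use is monitored only in those who stay, so that adherence is guaranteed by construction. The article does not support that. Sections 3.3 and 3.6 describe monitoring of all recruited participants. The conditional wording is one clause in the incentives section, and even there it fixes only retention or duration, not the engagement count that section 3.6 defines as adherence. This part is a contradiction to reconcile, not a settled design choice.

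A reader might also infer that an ineffective app would be bound to look effective. That does not follow either. Upward bias needs both attrition and a positive link between engagement and change, and the article quantifies neither. The zero-change null is also a simplification. The Introduction reports decline after graduation, so selection might only offset a fall. That answer is partial, because the pilot counts maintenance as success: a true decline of 0.24 SD combined with a selection effect of 0.24 SD would read as no change.

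It can be argued that the engaged subset matches a stated question, since the Introduction asks whether adherence is associated with benefit, and that a condensed article may leave further analysis sets to a fuller plan. The first argument supports keeping the subset as a secondary analysis, although restricting to stayers removes the low-use end which that association needs. The second does not remove the point, because the article does state a population for the efficacy evaluation, and it is the engaged one. It is also true that the pilot seeks only preliminary evidence, sets no go/no-go rule, and cannot separate the app's effect from time trend even with everyone analysed. That limits the consequence but does not justify adding selection to it.

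**Conclusion.** The point stands in two parts.

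First, the primary efficacy comparison is restricted by post-baseline engagement in a single-arm pilot. No all-enrolled analysis is described and selection is not acknowledged as a limitation. Upward bias is the expected direction, not a certainty. At an assumed correlation of 0.3 it is about 0.1 SD with 80% retained and 0.24 SD with 50% retained, with false-positive rates of about 10% and 22% against a nominal 5%. These sizes rest on assumed retention, an assumed correlation and a true mean change of zero.

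Second, section 3.5 contradicts sections 3.3 and 3.6 on whose usage is monitored. Following section 3.5 would defeat the retention question. Its expectation of 50 from about 50 assumes no attrition, at odds with the Discussion.

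**What to change.** 1. Reconcile section 3.5 with sections 3.3 and 3.6: monitor usage from download for everyone enrolled, and report adherence and retention with all enrolled as the denominator.
2. In sections 3.3 and 3.6 and Table 1, seek the follow-up questionnaire and push-up test from every enrolled participant regardless of app use. Make all enrolled the primary efficacy set and report the engaged subset as a labelled secondary analysis. Add a sensitivity analysis for missing follow-up. Keeping participants with only baseline data in the repeated-measures model does not by itself remove selection related to motivation; collecting their follow-up does.
3. Replace the expected 50 with about 50 enrolled and a realistic range of completers, with the resulting precision (half-width about 0.28 SD at 50 and 0.41 SD at 25). Add attrition and selection to the limitations.

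The cost is protocol wording, plus reminders and follow-up gift cards for low users. The estimated change will probably be less favourable, and the stated number of completers smaller.

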#### Healthy lifestyle score, physical fitness, and mental health outcomes

3.3.1

##### Healthy lifestyle score

3.3.1.1

Information will be collected using a questionnaire comprised of individually validated components via the Research Electronic Data Capture (REDCap) online survey software. These components include: tobacco use status, Mediterranean diet adherence screener (MEDAS) score (49, 50), physical activity level (51), sedentary behavior (measured in hours spent watching TV per week) and sleeping patterns (measured in daily sleeping hours and frequency of naps per week) (52).

The HLS score consists of seven dichotomously assessed items present in a healthy lifestyle (including: weight control [non-obese BMI], not smoking, Mediterranean diet adherence, regular physical activity, limited tv-watching, adequate sleeping, and napping). A value of 0 or 1 is assigned to each of the seven HLS components. Participants are assigned a value of 1 for each of the following: no smoking in the last 6 months, moderate-high physical activity (>16 METs-h/wk), high adherence to Mediterranean diet pattern (MEDAS ≥9 points) (50), BMI less than or equal to 30 kg/m^2^, time watching television (<2 h/d), adequate sleeping (7-8 h/d) and taking naps throughout the day (siesta or after lunch short nap); otherwise participants were assigned a value of 0. Total HLS scores range from 0 to 7 (with 7 reflecting the highest HLS and 0 the lowest) and has been previously associated with lower risk of prevalent hypertension and higher aerobic capacity among young firefighter recruits (9). Components of the HLS score (e.g. MEDAS score, sleep pattern, physical activity level, etc.) will also be assessed individually.

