### HLS app prototype

2.2

The HLS app prototype for mobile device platform(s) (IOS/Android) is intended to be used in future HLS interventions directed at new firefighters. Using firefighters’ direct input, existing scientific literature, and reliable online resources, this HLS app titled “Surviving & Thriving” will be designed and developed to help firefighters implement and maintain lifestyle habits that optimize their health and functional performance. The app will promote the combination of balanced nutrition, regular physical activity, restorative sleep, positive social and family connections along with resilience/stress-reduction strategies, and the avoidance of tobacco, binge-drinking, and other toxic substances. In order to accomplish this goal, the app will provide a wide array of multi-domain content (i.e. physical activity, sleep, nutrition, resilience), deliver weekly motivational messages, promote the use of a habit tracker, and facilitate user-interaction through team missions. The content of the HLS app has been visually depicted in our “Surviving and Thriving” app logo (**Figure 1**).

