### Covariates

3.4

Socio-demographic characteristics (i.e., age, sex, educational level, marital status) as well as behavioral health information will be collected via the online survey. Working conditions & fire department culture/policies will be measured post- app usage by means of “health culture” scores (**Table 1**). These scores rate the extent to which a new firefighter perceives that his/her department and co-workers value and promote healthy behaviors. Because we are unaware of any such previously validated instrument, with the input and oversight from our fire service expert panel, we have modified a set of questions from the Fire service Organizational Culture of Safety (FOCUS) survey with the addition of some questions on health-promoting environments used in other occupational settings (56, 57).

**Table 1 T1:** Data Collection during the Pilot Study Phase of the *Surviving & Thriving* app.

Study Measures	Pre-app usage: <1 year from Fire Academy graduation	Post-app usage: 3-6 months of app engagement
Healthy Lifestyle questionnaire	**X**	**X**
Physical Fitness Measure (i.e., 1-min pushups)	**X**	**X**
Mental Health: Depression/Trauma symptoms (BDI-PC, PHQ-9 and PCL-5)	**X**	**X**
“Health Cultures” scores: ratings of each fire station’s/fire department’s environments (working conditions, culture/policies) as to encouraging/discouraging healthy behaviors)	–	**X**

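### The smoking item of the primary HLS score looks back 6 months, but follow-up is at 3-6 months, so the item cannot gain from a quit made on the app and can gain from some quits made before it

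*Protocol article*

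**What the plan says.** Section 3.3.1.1 (Healthy lifestyle score) builds the score from seven yes/no items: "A value of 0 or 1 is assigned to each of the seven HLS components". The smoking item earns its point for "no smoking in the last 6 months".

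Section 3.3 (Pilot study phase) sets two assessments, "before using the HLS app and at the subsequent follow-up (i.e. 3-6 months after" the first. The instrument does not change between them: "participants will receive the same lifestyle and mental health questionnaires and fitness test at the two time points". The same section states that "we will conduct a small single arm trial", with about 50 participants. Table 1, in section 3.4, times the first assessment as "Pre-app usage: <1 year from Fire Academy graduation".

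Section 3.6 (Statistical analysis) states that the primary efficacy outcome "will be the changes in the HLS score" from before to after app use. Section 2.2 (HLS app prototype) lists among the behaviours that the app promotes "the avoidance of tobacco, binge-drinking, and other toxic substances".

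Nothing in the article shortens the smoking look-back at follow-up, or separates quits made on the app from quits made before it.

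**The concern.** A change score can respond to an intervention only if the follow-up value describes time after the intervention began. Here the smoking item's look-back is at least as long as the interval between the two visits. At any follow-up before month 6, part of the window lies before app start. Smoking in that part blocks the point, whatever the participant did afterwards.

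Two things are at stake in one of the seven items of the primary outcome. A behaviour that the app sets out to promote cannot raise the item when it starts on the app. And a rise that does occur reflects a quit that came before the app. With a single arm, no comparison group shows how many such rises would have happened anyway. For participants enrolled within 6 months of graduation, the credited quit may even date from academy training, whose benefits the pilot hopes to see maintained.

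**Working it through.** **Inputs.** Look-back L = 6 months (section 3.3.1.1). Baseline at time 0 and follow-up at T, with T from 3 to 6 months (section 3.3). Same instrument at both visits (section 3.3). Item worth 0 or 1 (section 3.3.1.1). n of about 50 (section 3.3). The article states no figure for this item's sensitivity or for smoking frequency, so there is nothing to reproduce first.

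**Scoring rule.** Let q be the time of last smoking in months from baseline (negative means before the app), with abstinence afterwards.
- Baseline item = 1 if 0 - q ≥ 6, that is q ≤ -6.
- Follow-up item = 1 if T - q ≥ 6, that is q ≤ T - 6.
- The item moves from 0 to 1 only if -6 < q ≤ T - 6.

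Since T - 6 ≤ 0 for every permitted T, no q > 0 satisfies the last line.

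| Follow-up T | Quits that move the item 0 to 1 (months before baseline) | Quits after app start that score |
|---|---|---|
| 3 | 3 to <6 | none |
| 4 | 2 to <6 | none |
| 5 | 1 to <6 | none |
| 6 | 0 to <6 | none |

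The one boundary case is a last cigarette on the baseline day itself with follow-up at exactly 6 months; it scores. Because T varies between participants, so does the credited window.

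**Relapse.** A participant with q ≤ -6 who smokes during app use goes from 1 to 0, and the item registers it. A participant who quit 2 months before baseline and then relapses goes from 0 to 0, and it does not. The item can therefore fall because of behaviour on the app, but only for those who held the point at baseline.

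**Size.** Each misscored participant changes the group mean by 1/50 = 0.02 points on the 0-7 scale. The missed mean gain equals the proportion of smokers times the proportion of them who quit on the app. Neither is in the article. Assuming 5-20% and 10-50%:
- low end: 0.05 × 0.10 = 0.005 points
- high end: 0.20 × 0.50 = 0.10 points

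Missed quits lower the mean change and credited earlier quits raise it, so the net direction is unknown.

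**With a shorter look-back.** In general the item moves from 0 to 1 if -L < q ≤ T - L. With L of about 1 month and T = 3, this is -1 < q ≤ 2. Quits in the first 2 months of app use now score, and the pre-app window shrinks from 3 to <6 months before baseline to less than 1 month before it. Scoring current smoking removes the pre-app window altogether.

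**The case against.** The timing arithmetic is hard to dispute, but several points on the other side carry weight.

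- **Not all of the credited gain is spurious.** A reader might infer that every 0-to-1 change before month 6 is caused by something other than the app. The documents do not support that. The recent quitter must also stay abstinent throughout app use, and the stated aim is to maintain as well as improve. What stands is that the quit came first and that a single-arm design cannot apportion the gain.
- **Not all earlier quits are credited.** Quits 6 months or more before baseline score 1 at both visits; quits less than 6-T months before it score 0 at both. Nor does the item register every relapse at once, as the working shows.
- **Tobacco is a minor theme.** Section 2.2 names it once. The four content domains in sections 2.2.1 to 2.2.4 do not describe a cessation component, and the Discussion expects change in nutrition, sleep, physical activity and resilience. A large lost cessation effect is therefore unlikely.
- **Some of the data may already exist.** Section 3.3.1.1 lists tobacco use status in the questionnaire and says components will also be examined singly. The exact questions are not shown, so current smoking may already be recorded. This does not repair the primary score, because the single item as defined keeps the 6-month look-back.
- **The score is an established one.** The article cites its association with prevalent hypertension and aerobic capacity in recruits. That is a reason to keep reporting it, but it does not show that the item can register change over 3-6 months.

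**Conclusion.** The point holds as a mismatch between three things that the article states: the 6-month look-back, the 3-6 month follow-up and the use of the pre-post change as primary outcome. For T < 6 months the item cannot rise because of a quit made on the app, and it rises for sustained quits made (6-T) to <6 months before baseline. This conclusion needs no assumption beyond the stated timings.

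Its size is probably modest: 0.02 points of mean change per misscored participant at n = 50, and 0.005 to 0.10 points of missed gain under smoking and quit rates that are assumed here. A reader might infer that the primary outcome as a whole is invalid. That would go too far: one item of seven is affected, only recent quitters and smokers are misscored, and no SD is given from which an effect on the test could be shown. The mismatch is still worth correcting, because it is a fixed rule that misreads change and it may not be recoverable if the timing of last smoking is not collected.

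**What to change.** For the pre-post HLS change, score smoking at both visits on current status or on a look-back shorter than the minimum 3-month follow-up, for example the past 30 days. Check that the tobacco questions capture this and the date of last smoking at both visits. Report the published 6-month version of the score as well, for comparability with the earlier work in recruits.

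The cost is at most one or two questionnaire items and one scoring line. There are two downsides: a small departure from the published score, and a short window that also credits brief abstinence. Reporting both versions covers these, and the date of last smoking lets a reader see which changes began on the app.
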